**Protocol Summary**

| **Short Title** | Postoperative Elbow rehabilitation |
| --- | --- |
| **Objectives** | This study aims to assess the efficacy of WeChat–based plus scene–graphics health education following open elbow arthrolysis. |
| **Study Design** | This study is a single-center, interventional, historical control study. |
| **Ethical Registration Number** | 2020–028 |
| **Clinical Research Registration Number** | ChiCTR2000036004 |
| **Study Center** | Shanghai sixth people’s hospital, China Shanghai |
| **Primary Outcome** | The primary outcome was the difference in elbow range of motion after 1-week, 6-weeks and 12-weeks post-operative. |
| **Secondary Outcome** | 1-week, 6-weeks and 12-weeks of Psysiological function in quality-of-life scores(SF-36), elbow function by using Mayo Elbow Performance Score(MEPS), assessing the incidence of complications through clinic manifestations and examination results. |
| **Population** | 112 patients diagnosed as elbow stiffness that need to undergo open elbow arthrolysis will be recruited and enrolled into the WeChat group (n=56) or the Control group (n=56). |
| **Study Duration** | 15 months |
| **Follow-up visit** | 1-week, 6-weeks and 12-weeks post-operative |
| **Intervention Group** | Received health education using WeChat and scene–graphics. The information in 4-part comics was shared via a WeChat public account. The patients got information from the account and had daily lessons during hospitalization, and online instruction in a WeChat group after discharge until 12 weeks post-operation. |
| **Control Group** | traditional health education  Received the usual health education provided by the hospital, which includes verbal instructions and electronic materials. Patients in this group did not receive any WeChat-based or scene-graphics education. |
| **Main Inclusion Criteria** | 1. Patients must be aged >18 years old.  2. Must have a diagnosis of elbow stiffness requiring surgical intervention.  3. Must be willing and able to provide informed consent.  4. Must be able to understand and communicate in Mandarin, as the WeChat public account and group will be conducted in these languages.  5. Must have access to a smartphone with WeChat application installed for the intervention group participants. |

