| **Result** | Elbow flexion angle: WeChat group 71.5 (SD 4.2) to 124.2 (SD 11.7) °; Control group 71.7 (SD 4.6) to 114.4 (SD 13.6) ° (diff 10 °, 95% CI 4.9–15.1, P <.001). Elbow extension angle : WeChat group 29.6 (SD 6.0) to 6.4 (SD 2.5) °; Control group 28.8 (SD 3.8) to 10.1 (SD 3.4) ° (diff -4.5 °, 95% CI -6.5– -2.5, P <.001). Forearm pronation angle: WeChat group 31.9 (SD 4.0) to 66.9 (SD 7.3) °; Control group 33.0 (SD 4.2) to 63.1 (SD 7.2) ° (diff 4.9 °, 95% CI 2.0 –7.8, P =.001). Forearm supination angle: WeChat group 30.2 (SD 3.7) to 71.8 (SD 4.8) °; Control group 30.4 (SD 4.1) to 64.2 (SD 9.8) ° (diff 7.7 °, 95% CI 4.4–11.0, P <.001). MEPI score: WeChat group 58.0 (SD 3.7) to 80.4 (SD 5.7); Control group 58.9 (SD 2.8) to 75.8 (SD 6.9) (diff 5.5 points, 95% CI 2.8–8.2, P <.001). SF - 36 score: WeChat group 44.4 (SD 6.6) to 82.0 (SD 7.1); Control group 44.0 (SD 6.4) to 75.0 (SD 11.2) (diff 6.6 points, 95% CI 2.6–10.6, P =.002). |

Content

[List of Abbreviations 1](#_Toc5648)

[Protocol Summary 1](#_Toc8973)

[1. Introduction and Rationale 5](#_Toc6776)

[1.1 Introduction 5](#_Toc12802)

[1.2 Rationale 8](#_Toc10032)

[2. Study Design and Purpose 10](#_Toc13487)

[2.1 Study Design 10](#_Toc9164)

[2.2 Study Purpose 10](#_Toc13211)

[3. Study Population 11](#_Toc16618)

[3.1 Enrollment Population 11](#_Toc9790)

[3.2 Inclusion and exclusion criteria. 11](#_Toc17452)

[3.3 Informed Consent 14](#_Toc24464)

[3.4 Early Withdrawal of subjects 15](#_Toc20744)

[3.5 Replacement of participant 15](#_Toc2086)

[3.6 Early termination of the study 15](#_Toc31974)

[3.7 Interim analyses 16](#_Toc23113)

[4.Study Procedures 16](#_Toc12649)

[4.1Participant recruitment 17](#_Toc14242)

[4.2 Blinding 17](#_Toc13786)

[4.3 Intervention 17](#_Toc11637)

[4.4 Study Duration 25](#_Toc16652)

[5.Data 29](#_Toc25472)

[5.1 Data Collection 29](#_Toc16174)

[5.2 Data Transmission 29](#_Toc4851)

[5.4 Data Storage 30](#_Toc4970)

[5.5 Data Sharing 30](#_Toc20005)

[5.6 Cancellation of Participation 30](#_Toc6979)

[5.7 Researcher Confidentiality 31](#_Toc26350)

[5.8 Data Retention Period 31](#_Toc10761)

[6. Safety 31](#_Toc28880)

[6.1 Related to the surgical site 31](#_Toc9447)

[6.3Abnormal rehabilitation progress 33](#_Toc1357)

[6.2 Safety of Data Collection 34](#_Toc27726)

[7. Study Monitoring 36](#_Toc25635)

[7.2 Collect patient's feedback 36](#_Toc26060)

[8. Ethical Considerations 36](#_Toc5706)

[Appendix 1. 38](#_Toc20883)

[Informed Consent 38](#_Toc12767)

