**2. Study Design and Purpose**

**2.1 Study Design**

The study was designed as a historical control study to assess the effectiveness of a WeChat-based health education program that incorporates scene-graphics in the rehabilitation process following open elbow arthrolysis.

The study was conducted over a period of 15months, with a total of 112 patients who underwent open elbow arthrolysis being enrolled. The patients were divided into two groups: the WeChat group, which received the WeChat-based plus scene-graphics health education, and the control group, which received traditional educational intervention. The primary outcome measure was the improvement in elbow range of motion (ROM) at the end of the 1-week, 6-weeks, 12-weeks post-operative period. Secondary outcomes included , the quality of life , elbow function and the rate of complications. Data were collected at baseline, at 1-week, 6-weeks, and 12-weeks postoperatively. The study aimed to determine whether the innovative educational approach could enhance patient recovery and engagement in rehabilitation, leading to better clinical outcomes.

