**4.4.3 Statistical Method**

SPSS Statistics version 26.0 (IBM Corp) was utilized for the data analysis. The chi-square test was used to analyze sex, disease side, and the incidence of postoperative complications. The collected data were subjected to a comprehensive statistical analysis to evaluate the effectiveness of the intervention on elbow stiffness. The normality of the data was first assessed using the Shapiro-Wilk test. For variables that satisfied the normality test, parametric statistical methods were employed, including the paired sample t-test for comparing pre-intervention and post-intervention values. For variables that did not meet the normality assumption, non-parametric tests, specifically the Wilcoxon signed-rank test, were utilized. The changes in elbow range of motion (ROM), the Mayo Elbow Performance Score (MEPS), and the Short Form-36 (SF-36) health survey scores at each time point were analyzed using repeated measures analyses of variance (ANOVA). The results were presented as mean ± standard deviation (SD) for continuous variables and as frequencies and percentages for categorical variables. In cases where the data were not normally distributed, median values and interquartile ranges (IQRs) were reported. The level of statistical significance was set at a two-tailed P value < .05. All statistical analyses were performed using appropriate software to ensure accuracy and to provide a robust interpretation of the study findings.

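### The reported group differences are unadjusted differences in change from baseline; adjusting for the baseline value would narrow all six intervals and move extension from -4.5 to about -3.8 degrees

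*Protocol*

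**What the plan says.** Section 2.1 frames the primary outcome as a gain: "The primary outcome measure was the improvement in elbow range of motion (ROM". Section 4.4.2 likewise compares range of motion with the preoperative measurement.

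On method, the Statistical Methodology row of the Protocol Summary names t-tests between groups and repeated measures ANOVA. Section 4.4.3 names within-patient paired t-tests or Wilcoxon tests, and says that the range of motion, MEPS and SF-36 "scores at each time point were analyzed using repeated measures analyses of variance (ANOVA". Neither place names the baseline value as a covariate.

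The Result row prints two means with SDs per group and one group difference with its interval. For extension, the WeChat group is "WeChat group 29.6 (SD 6.0) to 6.4 (SD 2.5" and the comparison is "Control group 28.8 (SD 3.8) to 10.1 (SD 3.4) ° (diff -4.5 °, 95% CI -6.5– -2.5, P <.001". For pronation the means are "WeChat group 31.9 (SD 4.0) to 66.9 (SD 7.3) °; Control group 33.0 (SD 4.2) to 63.1 (SD 7.2". The row does not say how the differences or the intervals were computed. Nor does it label the visit of the second mean, which is read here as 12 weeks. Patients were "enrolled into the WeChat group (n=56) or the Control group (n=56", and the Allocation row says that the groups were formed by admission period.

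**The concern.** A change score subtracts the whole baseline value from the end value. If the baseline value predicts the end value only weakly, the subtraction does two things. It carries nearly all of the baseline gap between the groups into the estimate, and it adds the baseline variance to the error. Weak prediction is plausible here, because surgery lies between the two measurements and section 1.1 gives it common targets (flexion above 130 degrees, extension below 10).

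What is at stake is the size and precision of the headline estimates, including two of the four primary-outcome angles (extension and pronation). The baseline values have already been collected, so adjusting for them needs no new data.

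**Working it through.** **Inputs.** Means, SDs, differences and intervals come from the Result row, for example "Control group 71.7 (SD 4.6) to 114.4 (SD 13.6) ° (diff 10 °, 95% CI 4.9–15.1, P <.001" for flexion and "Control group 33.0 (SD 4.2) to 63.1 (SD 7.2) ° (diff 4.9 °, 95% CI 2.0 –7.8, P =.001" for pronation. Each arm has 56 patients. The number analysed is not stated, so 56 is an assumption and is varied below. The t quantile with 110 degrees of freedom is 1.982.

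**Step 1: reproduce the stated effect.** Difference in change for extension = (6.4 - 29.6) - (10.1 - 28.8) = -23.2 + 18.7 = -4.5, as stated. The end-value gap is 6.4 - 10.1 = -3.7 and the baseline gap is 29.6 - 28.8 = +0.8. The same sum reproduces the other five outcomes (supination gives 7.8 against 7.7, which rounding explains).

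**Step 2: correlation implied by the stated interval (extension).**
- SE = 2.0 / 1.982 = 1.009. The sum of the two change-score variances is 56 × 1.009² = 57.0.
- That sum also equals the sum of the four squared SDs minus 2r × (sum of baseline SD × end SD). Here 6.0² + 2.5² + 3.8² + 3.4² = 68.25, and 6.0 × 2.5 + 3.8 × 3.4 = 27.92.
- r = (68.25 - 57.04) / (2 × 27.92) = 0.20.

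**Step 3: baseline-adjusted effect (extension).**
- Pooled within-group slope = 0.20 × 27.92 / (6.0² + 3.8²) = 0.11.
- Adjusted difference = -3.7 - 0.11 × 0.8 = -3.8.
- Residual variance = (2.5² + 3.4²)/2 - 0.111² × (6.0² + 3.8²)/2 = 8.59. Half-width ≈ 1.98 × √(8.59 × 2/56) = 1.1, so the interval is about -4.9 to -2.7.
- Variance of the change score relative to the adjusted analysis = (57.04/2) / 8.59 = 3.3.

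**Step 4: all six outcomes, same method, 56 per arm.**

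| Outcome | End gap | Baseline gap | Stated | Implied r | Slope | Adjusted | Half-width, stated / adjusted | Variance ratio |
|---|---|---|---|---|---|---|---|---|
| Flexion | 9.8 | -0.2 | 10 | -0.05 | -0.13 | 9.8 | 5.1 / 4.8 | 1.15 |
| Extension | -3.7 | +0.8 | -4.5 | 0.20 | 0.11 | -3.8 | 2.0 / 1.1 | 3.3 |
| Pronation | 3.8 | -1.1 | 4.9 | 0.16 | 0.28 | 4.1 | 2.9 / 2.7 | 1.17 |
| Supination | 7.6 | -0.2 | 7.7 | -0.05 | -0.09 | 7.6 | 3.3 / 2.9 | 1.31 |
| MEPI | 4.6 | -0.9 | 5.5 | -0.03 | -0.05 | 4.6 | 2.7 / 2.4 | 1.30 |
| SF-36 | 7.0 | +0.4 | 6.6 | 0.14 | 0.19 | 6.9 | 4.0 / 3.5 | 1.32 |

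The weakest adjusted effect is pronation, at 4.1 / (2.7/1.98) = 3.0 standard errors, so all six stay significant.

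**Step 5: how firm this is.** Rounding of the extension interval (half-width 1.95 to 2.05) gives r from 0.15 to 0.25 and an adjusted effect from -3.77 to -3.81. Assuming r anywhere from 0 to 0.5 gives -3.7 to -3.9. Even r = 1 allows a slope of only 27.92 / 50.44 = 0.55, hence -3.7 - 0.55 × 0.8 = -4.1.

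The other outcomes depend more on the number analysed. At 50 per arm the pronation slope is 0.48 (0.53 with interval rounding) and the adjusted effect 4.3. MEPI becomes 4.8, and the flexion half-width is 5.0 against 5.1, almost no gain.

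**The case against.** The strongest reply is about design. A reader might infer that the printed effects are wrong, because a change score is valid only when the baseline slope is 1. That does not follow here. The groups were formed by admission period. With such groups a change score is unbiased if both would have changed equally without the intervention, whatever the within-group slope. The adjusted analysis needs a different assumption: no group difference in end value, given baseline, without the intervention. Neither can be tested from the Result row. The document also defines its outcome as improvement, and its arithmetic for that quantity is right. This stands, and it limits the point to precision and to sensitivity to the baseline gap.

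The reply is also right that no conclusion changes. Every adjusted value lies inside its printed interval, flexion and supination move by 0.2 or less, and SF-36 moves upward, so a general claim of overstatement would be false. The document gives no important-difference threshold against which to judge shifts of 0.7 to 0.9.

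A reader might further infer that repeated measures ANOVA will lose many patients through missed visits. The protocol gives no missed-visit rate, and the handling of missing data may sit in an analysis plan that is not shown. That inference is not made here.

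A separate analysis plan might also name a baseline covariate. It would not alter the printed differences, which are unadjusted.

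**Conclusion.** The point holds as an improvement to the analysis, not as a demonstrated error and not as something that must be corrected before the results can be read. The printed differences are unadjusted differences in change. At the correlations that the document's own figures imply, the change score carries about 0.7 of the 0.8 degree baseline gap into extension, about 0.8 of 1.1 degrees into pronation, and essentially all of the 0.9 points into MEPI. The gain in precision is large for extension (variance ratio 3.3) and modest elsewhere (1.15 to 1.32).

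The assumptions are 56 analysed per arm, t-type intervals on the change score, one baseline-to-end correlation for both arms, and end values that are the 12-week values. The extension result is stable when the first of these and the size of the correlation are varied. The other five are less so. The adjusted figures remain open to confounding by admission period.

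**What to change.** In section 4.4.3 and in the Statistical Methodology row, add a between-group comparison of the post-operative values that adjusts for baseline. This can be ANCOVA at 12 weeks, or a mixed model over the 1-, 6- and 12-week values with baseline × visit and group × visit terms. In the Result row, print the adjusted difference with its 95% CI for all six outcomes beside the present change-score figures. State how each was computed and how many patients were analysed, and label the adjusted analysis as added after results were known.

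The cost in work is one further run on existing data. The cost in interpretation is real: some estimates become smaller, the added analysis is post hoc, and the narrower intervals could suggest more certainty than an unblinded comparison of two admission periods supports. For that reason the adjusted figures should stand beside the stated analysis, with a sentence saying that they do not remove other confounding.

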**1.1 Introduction**

Normal elbow mobility serves as an essential and fundamental condition in our daily life. It is the cornerstone that enables us to perform a wide array of activities with ease. Elbow stiffness, unfortunately, is a rather prevalent issue, and its incidence is surprisingly high. In fact, it has been found to affect as many as 56% of individuals subsequent to elbow trauma [1, 2]. This condition is marked by a significant limitation in the range of motion or rotation of the elbow joint, which in turn results in the inability of the elbow to fulfill the patient's diverse requirements for daily activities, including but not limited to simple tasks like dressing and eating, as well as more complex ones related to work and various forms of entertainment [3, 4].

Open elbow arthrolysis (OEA) has emerged as the most commonly employed surgical intervention in such cases. Extensive research and clinical practice have demonstrated its remarkable efficacy in restoring the elbow's function and range of motion [3, 4]. During the surgical procedure, surgeons can achieve the release of the elbow by carefully removing bony impediments or scar tissue within the olecranon fossa. This meticulous process aims to adjust the flexion of the elbow to more than 130° and the extension to less than 10°, thereby optimizing the joint's functionality [5, 6].

However, it is of utmost importance to note that postoperative rehabilitation plays an indispensable role in the overall process of elbow function recovery [4 - 8]. A substantial and ever - growing body of evidence clearly indicates that when postoperative rehabilitation is carried out in a timely and appropriate manner, it paves the way for highly favorable outcomes. On the contrary, if the rehabilitation process is inadequate, it can lead to a host of severe problems related to elbow recovery [4 - 8]. These problems are not limited to just a minor setback but can involve various postoperative complications that can significantly impact the patient's quality of life. Such complications include heterotopic ossification (HO), which can cause additional pain and restricted movement. Additionally, new onset or exacerbation of ulnar nerve symptoms can occur, leading to nerve - related issues such as numbness or weakness in the arm. Moreover, there is a significant risk of repeat elbow stiffness, which can be a major setback for the patient's recovery journey [3, 9 - 11].

According to incomplete yet telling statistics, the situation is quite concerning. The incidence of postoperative elbow issues stands at a staggering 56 - 87% [5]. The probability of renewed elbow stiffness is also alarmingly high, ranging from 8.4 - 47% [5, 6]. Furthermore, the rate of secondary surgery, which is often required to address these complications, is between 10 - 34% [6, 7]. To make matters worse, the rate of patient dissatisfaction due to these issues reaches 21% [7]. These figures clearly emphasize the need to enhance the precision of postoperative rehabilitation and ensure better patient adherence to the rehabilitation protocols.Nevertheless, achieving perfect postoperative rehabilitation is an extremely challenging task. This is primarily because the process is not only prolonged but also highly intricate [6, 12, 13]. Standard postoperative rehabilitation typically spans a period of one year and is systematically divided into three distinct phases [6, 14, 15]. The first phase, known as the acute phase, commences on the very first day after the surgery and extends up to 6 weeks. During this initial and crucial period, the rehabilitation process involves a series of passive, assisted, and active elbow flexion and extension motions [6, 14, 15]. To be more specific, on the first day, patients are recommended to start with 30 such movements. As the days progress, this number is increased by 30 each day until a total of 300 movements are achieved on a daily basis [6, 14]. The second phase, which lasts from 6 weeks to 3 months after the surgery, is designated as the subacute phase. During this period, the daily requirement for these elbow movements remains at 300, ensuring a consistent and continuous rehabilitation effort [14].The third and final phase, the functional phase, lasts from 3 months up to one year after the operation. This phase is particularly significant as it involves the addition of weight - bearing practices to the rehabilitation routine. Moreover, the intensity of the rehabilitation activities is gradually increased on a daily basis during this period [14, 15].It is important to recognize that in addition to the initial rehabilitation process that takes place within the hospital environment, patients are also required to continue their rehabilitation efforts at home. This home - based rehabilitation is an integral part of the overall recovery process. As a result, having a comprehensive and highly accurate grasp of the relevant knowledge related to rehabilitation is absolutely crucial for ensuring effective rehabilitation outcomes [13, 14, 16].

However, in recent times, there has been a significant increase in the prevalence of Enhanced Recovery After Surgery (ERAS) protocols [17 - 18]. While these protocols have brought about several benefits, one of the consequences has been a reduction in the duration of hospital stays. This reduction, unfortunately, has created a new challenge as traditional health education methods have proven to be insufficient for patients to gain the adequate amount of knowledge required for successful rehabilitation. Therefore, there is an urgent need to develop more efficient and feasible health education approaches to address this critical issue.

**1.2 Rationale**

The rationale behind the development of these new approaches is to ensure that patients are well-equipped with the necessary knowledge and skills to continue their rehabilitation process effectively at home. This is particularly important given the shortened hospital stays and the critical role that self-management plays in the overall recovery. The new health education methods must be designed to be easily accessible, engaging, and tailored to the individual patient's needs and learning pace. They should also incorporate feedback mechanisms to monitor patient progress and adapt the educational content accordingly. By addressing these needs, it is hoped that patients will be able to achieve better rehabilitation outcomes and a higher quality of life post-surgery.

In recent years, telemedicine services have witnessed a growing popularity in the realm of health education. Healthcare professionals leverage electronic information and communication technology to offer and support healthcare services to patients, without being restricted by the patients' location or transportation issues [19]. WeChat, being one of the most widely and frequently utilized free platforms in China [20 - 22], is capable of providing convenient telemedicine services. It can accommodate various data types including text, voice calls, videos, and images, enabling convenient and clear communication [21], thereby attracting a large number of users. By the end of 2020, there were 1.2 billion monthly active users globally [22, 23], and these users are more vigorously seeking online healthcare and health information exchange [24]. A prior survey indicated that one - third of the participants regularly read health - information - related articles on WeChat [25], and 98.53% of them used WeChat to search for health information [24]. This platform has been applied in the health management of numerous conditions such as public health literacy [26], cancer [27, 28], asthma [29], chronic obstructive pulmonary disease [30], hypertension [31], myopia [32], coronary artery disease [33], etc. Nevertheless, no research has concentrated on its application in the postoperative rehabilitation of patients with elbow stiffness.

Medical humanities is an interdisciplinary multifaceted field that combines scientific knowledge and skills with respectful, compassionate care that is sensitive to the values, autonomy, and cultural backgrounds of patients and their families[34]. Medical comics are among the numerous approaches in medical humanities that have the potential to address challenging situations within medical settings [34,35]. Medical comics have been utilized to promote adolescent peer support and healthy sexual behaviors [35], raise awareness about diabetes [36], improve the quality of palliative care [37], and increase whole-body donation awareness[38]. Scene-based graphics are a type of approach that can simplify knowledge points into comics and can deliver messages in an engaging manner through various humorous scenarios so that the knowledge becomes easily understandable and memorable. The graphics have converted activities of daily living scales into comics for rapid and straightforward evaluation [39]. Additionally, interactive games have been added into it which align with the corresponding knowledge [40]. Interactive games can be designed according to the key point of knowledge and the characteristics of the learners, which can encourage participants to engage in learning and apply their knowledge more skillfully. However, this approach is in the initial stage and is rarely employed in postoperative rehabilitation. This study was conducted as a historical control study to evaluate the efficacy of WeChat-based plus scene-graphics health education in the postoperative rehabilitation of open elbow arthrolysis.

